### Statistical analysis

Analyses will use methods appropriate for the cluster randomised trial design, giving each cluster equal weight. Quantitative outcomes will be summarised as the mean for each cluster and the difference of means for the intervention versus standard of care arm. For binary outcomes or rate outcomes, the overall risk (rate) for each cluster will be calculated, as well as the ratio for the intervention versus standard of care arm. Given the overall randomisation was conducted using two strata (20 and four clinics in each stratum), the standard error for each effect measure will take into account stratified randomisation. An adjusted analysis will be conducted if, after visual inspection, imbalance by study arm in patient- or clinic-level factors is observed, to help reduce variability across clinics with respect to primary and secondary outcomes.

Subgroup analyses will be conducted for the primary outcome for baseline CD4 count (<50 or ≥50 cells/μL), previous tuberculosis history (from self-report; no previous or previous tuberculosis), baseline BMI (<18.5 or ≥18.5 kg/m^2^) and baseline haemoglobin (<8 or ≥8 g/dL). A statistical analysis plan documents the analysis of all trial outcomes.

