### Randomisation

The initial randomisation of 20 clinics was based on restriction, common in cluster randomised trials with a small number of clusters [19], and based on having reasonable balance, separately, for mean CD4 count, peri-urban/rural location of the clinic and the total number of new ART initiations per month. Using these criteria, 11,160 (6.0%) of the 184,756 possible allocations for randomising 20 clinics to two arms (ratio of 1:1) were identified. The validity of this restriction was checked for each allocation by comparing the number of times a cluster appeared in the same arm with each other cluster. There was no extreme imbalance and this restriction was assumed to be valid. The randomisation was organised by a statistician. In a public ceremony with study clinics represented by clinic managers and other HIV and TB programme staff, one allocation was chosen at random. Due to the revision in sample size, a second public randomisation took place 14 months later, where four additional clinics were randomised in a ratio 1:1 to the intervention or standard of care arm.

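### The stated standard error reflects the two strata but not the restricted draw of the first 20 clinics; if the restriction factors predict mortality, the primary test is modestly conservative

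*Protocol article*

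**What the plan says.** **Allocation (Protocol article, Randomisation).** For the first 20 clinics, "11,160 (6.0%) of the 184,756 possible allocations for randomising 20 clinics to two arms (ratio of 1:1) were identified". The criterion was reasonable balance, "separately, for mean CD4 count, peri-urban/rural location of the clinic and the total number of new ART initiations per month". One permitted allocation was drawn at random. Fourteen months later, "four additional clinics were randomised in a ratio 1:1 to the intervention or standard of care arm"; no restriction is described for that second draw.

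**Analysis (Protocol article, Statistical analysis).** The general rule is: "Analyses will use methods appropriate for the cluster randomised trial design, giving each cluster equal weight". On variance, the text names the two strata of 20 and four clinics as its reason and concludes that "the standard error for each effect measure will take into account stratified randomisation". On covariates: "An adjusted analysis will be conducted if, after visual inspection, imbalance by study arm in patient- or clinic-level factors is observed". The restriction is not mentioned in this section, which refers to a separate statistical analysis plan for the analysis of all outcomes.

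**The concern.** The section derives its standard error from how the clinics were randomised, but it names only one of the two features of that randomisation. Restriction limits how far the arms can differ by chance on the three factors, so the effect estimate varies less from draw to draw. The between-clinic variation due to those factors nevertheless stays in the residual variance of an unadjusted analysis. The standard error then describes a free draw within each stratum, which is not the draw that was made.

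The conditional adjustment is unlikely to close this gap. It depends on visible imbalance, and the restriction makes visible imbalance less likely for exactly these factors in 20 of the 24 clinics.

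At stake are a confidence interval for mortality somewhat wider than the design warrants, a test that runs below its nominal level, and a few points of power in a trial of 24 clusters.

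**Working it through.** **Inputs from the Protocol article (Sample size considerations; Randomisation).** 25 deaths per 100 person-years in the control arm; coefficient of variation k of 0.2 to 0.25; 5% with unknown vital status; originally 10 clinics per arm with 175 patients each; revised to 12 per arm with a harmonic mean of 109.

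**Assumptions, not in the documents.** Two-sided 5% test. R², the share of true between-clinic variance in mortality explained by the three factors, is varied from 0 to 0.75.

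**1. Allocation counts.** C(20,10) = 184,756, and 11,160 / 184,756 = 6.04%. Both agree with the text.

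**2. The plan's own power.** The Hayes-Bennett formula for rates gives z_β = √[(c − 1)(λ0 − λ1)² / V] − 1.96, with V = (λ0 + λ1)/y + k²(λ0² + λ1²). Person-years per clinic are y = 175 × 0.95 × 0.5 = 83.125. For a 40% reduction at k = 0.2, V = 0.4/83.125 + 0.04 × 0.085 = 0.00821, so z_β = √(9 × 0.01/0.00821) − 1.96 = 1.35 and power is 91.2%.

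| Case | Stated | Recomputed, original design | Recomputed, 12 per arm, 109 per clinic |
|---|---|---|---|
| 40% reduction, k = 0.2 | 91% | 91.2% | 88% |
| 40% reduction, k = 0.25 | 85% | 84.6% | 83% |
| 35% reduction, k = 0.2 | 81% | 81.2% | 77% |

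The formula contains no term for restriction, so the stated power does not depend on it.

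**3. How much restriction can matter.** In the revised design y = 109 × 0.95 × 0.5 = 51.775. The variance of a control clinic's rate is 0.25/51.775 = 0.00483 from chance, plus (0.25k)² between clinics: 0.0025 at k = 0.2 and 0.0039 at k = 0.25. The between-clinic share f is therefore 34% or 45%. The 20 restricted clinics carry 5/6 of the variance of the estimate: (20/24)² × 2/10 = 0.139 of a total of 0.167. If restriction balanced the factors perfectly in those clinics, the ratio of stated to true standard error would be 1/√(1 − (5/6) R² f). At R² = 0.5 this is 1.08 (k = 0.2) or 1.11 (k = 0.25). With the 20-degree-of-freedom critical value of 2.086, the true type I error would be about 3.6% or 3.2%.

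**4. Simulation.** Twenty clinics restricted to about 6% of allocations on three equally prognostic factors, four clinics unrestricted, Poisson deaths, 109 patients per clinic, 5% loss. The strata-only t-test on log clinic rates was compared with a cluster-level regression that also includes the three factors. Ranges and pairs run over k = 0.2 and 0.25.

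| R² | Type I error, strata only | Stated/true standard error under the null | Power for a 40% reduction, strata only → adjusted |
|---|---|---|---|
| 0 | 4.9–5.1% | about 1.01 | 86 → 85%; 81 → 79% |
| 0.25 | 4.0–4.3% | 1.02–1.05 | 87 → 88%; 82 → 83% |
| 0.5 | 3.0–3.4% | 1.08–1.09 | 87 → 89%; 83 → 87% |
| 0.75 | 2.3–2.6% | 1.12–1.17 | 88 → 92%; 82 → 90% |

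Monte Carlo error is about 0.3 points for type I error and 0.6 to 0.8 points for power. A separate run of the same design gave 3.5 to 4.1% type I error at R² = 0.5, so 3 to 4% is a fair statement there. At k = 0.25, a permutation test over the permitted allocations held about 5%. It raised power for a 40% reduction from 82.9% to 84.7% at R² = 0.3 and from 83.2% to 85.9% at R² = 0.5. At R² = 0 it costs essentially nothing.

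**The case against.** The strongest reply is that the text does not say the standard error reflects the strata alone. The article is a condensation, promises methods suited to the design, and refers to an analysis plan that is not shown. Adjustment for the restriction factors may well be in that plan. This stands as a caution: if so, the article's wording only needs to be aligned with it. It does not remove the point. The section gives a positive rule for the variance, justified by the randomisation, and makes covariate adjustment conditional on observed imbalance. That rule does not fit the draw described under Randomisation.

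The second reply is that the size is unknown, and this stands in full. The documents give no R². The sample size section argues for limited between-clinic variation because every participant has a CD4 count of 150 cells/μL or less, and nothing links the number of monthly ART initiations to mortality. What the documents offer in favour of a non-zero R² is indirect: lower mortality at CD4 counts above 150, distance as a barrier to ART in rural areas, and higher mortality when ART is delayed. None of this gives a clinic-level figure.

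A reader might infer that the planned interval and test are certainly too conservative, or that the precision gained by restriction is lost. Neither follows. With R² near zero nothing changes. With R² above zero the estimate still varies less and the arms are still balanced; only the standard error fails to credit this. Nor is validity threatened: type I error does not exceed 5% beyond simulation error, and no stated power figure fails on this account.

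**Conclusion.** The point holds as a modest, conditional one. The stated variance rule covers the stratification but not the restriction, and the adjustment that could make up the difference is tied to a trigger that restriction makes unlikely to fire. If the three factors explain 25 to 30% of between-clinic variance, the primary test runs at roughly 4%, and about 1 to 2 points of power are forgone for a 40% reduction. At 50% it runs at 3 to 4%, with about 2 to 4 points forgone. Larger losses, of about 4 to 8 points, need an R² near 0.75. At zero there is no effect.

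These figures assume a two-sided 5% level, k of 0.2 to 0.25, equal prognostic weight for the three factors, a common balance threshold admitting about 6% of allocations, and no restriction on the four added clinics. The planned analysis is valid and errs on the safe side.

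**What to change.** In the Statistical analysis section, prespecify one of the following for the primary outcome, and report the stratified unadjusted result alongside it:

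- **Adjusted analysis.** A cluster-level analysis adjusted for mean CD4 count, peri-urban/rural location, monthly ART initiations and stratum, whatever visual inspection shows. The cost is three degrees of freedom. If the factors are not prognostic, this loses about 1 to 3 points of power (86 to 85% and 81 to 79% in the simulation).
- **Permutation test.** A test on the equal-weight clinic log rates over the permitted allocations, with the confidence interval by test inversion. If the second draw was unrestricted, these number 11,160 × C(4,2) = 11,160 × 6 = 66,960; if it was restricted, the count must be changed. The cost is a less familiar interval.

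The permitted allocations were already enumerated for the randomisation, so either option needs only wording and a little code. No new data or participants are required. If the analysis plan already contains one of these, a sentence in this section saying so is enough.

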## Methods/design

### Study design

The study is an open, pragmatic two-arm cluster randomised superiority trial, with primary health clinics as the unit of randomisation. The intervention is integrated into routine clinic activities as far as possible: study staff implement the algorithm, and all other aspects of care for the patient are delivered by clinic staff.

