### Trial outcomes

The primary outcome is all-cause mortality measured over a six-month period following enrolment. Secondary outcomes are (i) duration of hospital admission in the first six months after enrolment, (ii) time from enrolment to ART start, (iii) proportion of patients retained in HIV care and (iv) serious and severe adverse events in specified categories as defined by the study (particularly hepatotoxicity, hypersensitivity, peripheral neuropathy and nephrotoxicity). The study has also defined economic outcomes relating to measuring cost-effectiveness which include total diagnostic cost of the study cohort in intervention and control arms, as well as incremental diagnostic, treatment and per disability-adjusted life year (DALY) costs of the intervention compared to control from a provider perspective, over the six-month follow-up period.

Vital status at six months from enrolment will be ascertained from patient interview and medical records, and supplemented with information from the participant’s nominated next of kin for those lost to follow-up, and the South African mortality registration for participants with a South African identification number. If necessary, a trial endpoints committee will be convened, masked to study arm, to assign death endpoints where there are discrepant dates of death. Secondary outcomes will be measured using a combination of data from patient interview and medical records, abstracted at two and six months from enrolment. A substudy among study participants who die is being conducted, using needle and verbal autopsy methods to ascertain causes of deaths.

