Assuming 10 clinics per arm, 175 patients per clinic, 5% individuals whose vital status could not be ascertained at six months, estimated mortality of 25/100 person-years in the standard of care arm and coefficients of variation of 0.2 and 0.25, there would be 91% and 85% power to assess a 40% reduction in mortality, respectively. If the coefficient of variation is 0.2, there would be 81% power to assess a 35% reduction in mortality.

After enrolling participants for six months we established that for some clinics, the target of 175 patients per clinic was unlikely to be achieved, and so the sample size calculations were revised. Assuming a harmonic mean of 109 patients per clinic, by randomising an additional four clinics, the study maintained similar power and effect sizes as with the original calculation.

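### The adjusted analysis is triggered by visible imbalance between arms, but its stated purpose, less variability between clinics, depends on whether a factor is prognostic

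*Protocol article*

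**What the plan says.** The Statistical analysis section of the Protocol article plans cluster-level comparisons with equal weight per clinic and a standard error that respects the two randomisation strata (20 and four clinics). On covariates it says: "An adjusted analysis will be conducted if, after visual inspection, imbalance by study arm in patient- or clinic-level factors is observed". The same sentence gives the reason: "to help reduce variability across clinics with respect to primary and secondary outcomes". The rule therefore reaches the primary endpoint, defined under Trial outcomes: "The primary outcome is all-cause mortality measured over a six-month period following enrolment".

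The Randomisation section says the allocation of the first 20 clinics was restricted, "based on having reasonable balance, separately, for mean CD4 count, peri-urban/rural location of the clinic and the total number of new ART initiations per month". No restriction is described for the four clinics added later. Under Study design: "The study is an open, pragmatic two-arm cluster randomised superiority trial, with primary health clinics as the unit of randomisation".

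The article refers to a statistical analysis plan that is not shown. It may list covariates and name the leading estimate, so their absence here is not a finding. The trigger itself is fixed in the article.

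**The concern.** The trigger and the purpose call for different rules. Variability between clinics falls when a covariate is prognostic and varies from clinic to clinic. A difference between arms is neither necessary nor sufficient for that. A strongly prognostic factor that happens to be balanced would be left out and its precision lost. A weak factor that looks imbalanced would be brought in for little gain.

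Two features sharpen this. First, restriction makes mean CD4 count, location and ART volume, the factors thought important enough to design on, less likely than others to look imbalanced at clinic level. Second, judging by eye has no reproducible threshold, so two analysts could look at the same baseline table and decide differently. At stake is precision in a trial with only 24 clusters, and a clear answer to which mortality estimate counts.

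**Working it through.** **1. Reproduce the plan's power.** The inputs come from Sample size considerations. The original design had ten clinics in each arm with 175 participants apiece, and allowed for 5% with unknown six-month vital status. For the event rate and clustering it used "estimated mortality of 25/100 person-years in the standard of care arm and coefficients of variation of 0.2 and 0.25". The standard cluster rate formula, with two-sided alpha of 0.05 assumed because none is stated, is

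power = Φ( √(c−1)·(λ0−λ1) / √[(λ0+λ1)/y + k²(λ0²+λ1²)] − 1.96 )

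Here c = 10, λ0 = 0.25, y = 175 × 0.95 × 0.5 = 83.1 person-years per clinic, and k is the coefficient of variation.
- 40% reduction, k = 0.20: variance term 0.40/83.1 + 0.04 × 0.085 = 0.00821; power 91.2%.
- 40% reduction, k = 0.25: 0.00481 + 0.0625 × 0.085 = 0.01012; power 84.6%.
- 35% reduction, k = 0.20: power 81.2%.

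The article says "there would be 91% and 85% power to assess a 40% reduction in mortality, respectively", and 81% for the third case. The formula is therefore a fair basis for what follows.

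**2. What adjustment could save.** For the revised design (harmonic mean of 109 patients per clinic, 12 clinics per arm), y = 109 × 0.95 × 0.5 = 51.8. Take λ = 0.20, the midpoint of 0.25 and 0.15. The variance of a clinic rate is λ/y + k²λ².
- Sampling part: 0.20/51.8 = 0.00386.
- Between-clinic part: 0.0016 (k = 0.20) or 0.0025 (k = 0.25), which is 29% or 39% of the total.
- If covariates explain 20–60% of the between-clinic part, total variance falls by between 0.20 × 29% ≈ 6% and 0.60 × 39% ≈ 24%. Arm imbalance does not enter the calculation.

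In power terms, for a 40% reduction with 12 clinics per arm: cutting k from 0.25 to 0.20 (36% of between-clinic variance explained) raises power from 83% to 88%. Cutting k from 0.20 to 0.15 (44% explained) raises it from 88% to 92%.

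**3. How arbitrary the trigger is.** With 12 clinics per arm, the chance difference in an unrestricted clinic-level factor has standard error √(2/12) = 0.41 SD. It exceeds 0.25 SD in about 54% of allocations and 0.5 SD in about 22%. The unstated threshold thus largely decides whether adjustment happens.

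**4. Simulation of the rule.** The setting was 12 v 12 clinic summaries, unstratified, with one covariate of correlation ρ with the outcome, 40,000 runs per scenario, and imbalance defined as above 0.25 or 0.5 SD. All of these inputs are assumptions.

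| | ρ = 0.3 | ρ = 0.5 |
|---|---|---|
| Power, never adjusted | 80% | 80% |
| Power, adjusted only on imbalance | 80–81% | 83–85% |
| Power, always adjusted | 82% | 88% |
| Type I error, rule as single test | 4.5% | 3.7–3.9% |
| Type I error, better of unadjusted and triggered | 5.4–6.0% | 5.5–6.2% |

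A run at ρ = 0.7 gave 97% power when always adjusted against 86–91% under the rule. That is beyond what the planning figures allow: 0.7² = 49% of total variance, more than the 29–39% that lies between clinics. The 6–24% range in step 2 corresponds to ρ of about 0.24 to 0.49.

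A second simulation used two to four covariates, each correlated 0.2–0.35 with outcome (8,000 runs per scenario). It gave 2.8–4.8% for the rule as a single test and 5.6–6.8% for the better of the two results.

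**The case against.** The strongest defence is that the unadjusted comparison is always computed and the adjusted one only added, and that the unshown analysis plan may supply the covariate list, the threshold and the leading estimate. All of that may be so. It leaves the trigger standing, because an analysis plan that follows this sentence inherits it.

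The restriction argument is also only partial. It balanced clinic-level mean CD4 count at randomisation, in 20 of 24 clinics, and CD4 among enrolled patients can still differ by arm. The precision gain rests on assumed values and is about two power points at ρ = 0.3.

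Three stronger readings are tempting, and the document does not support them.
- A reader might infer that the choice is made with outcomes in view. The text describes inspection of patient and clinic factors by arm. An open design does not show that mortality by arm is seen when the choice is made.
- A reader might infer that the covariates are picked on sight. The text makes whether to adjust depend on the data; it does not say how the candidate list is formed.
- A reader might infer that recruitment by staff who know the allocation condemns the trigger. Case-mix differences arising that way are what an imbalance trigger would tend to catch. They argue for adjustment in general, not against this rule in particular.

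**Conclusion.** The point holds as a mismatch between rule and purpose. Adjustment is tied to visible imbalance, while the stated aim is precision, and precision is lost when the arms look balanced. The possible saving is about 6–24% of clinic-rate variance, assuming covariates explain 20–60% of the between-clinic part and the planned coefficients of variation hold. In simulation the rule loses part or all of the power gain.

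The type I error concern is minor. A reader might expect inflation to 8–12%, but that needs a free search over models, which the article does not describe. As a single test the rule is conservative, and choosing the better of the two results costs about one to two percentage points. The change is worth making because it is cheap and removes an avoidable judgement from the primary comparison; the unadjusted analysis remains valid without it.

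**What to change.** Drop the visual-inspection trigger. Before data are viewed by arm, specify in the analysis plan one adjusted analysis that is always done:
- **Method:** two-stage and cluster-level. Fit an individual-level Poisson or logistic model without the arm term, then compare clinic observed-to-expected ratios between arms within the two randomisation strata.
- **Covariates:** a short prognostic list available in both arms, for example individual CD4 count, BMI, age, sex and previous tuberculosis, plus very few of the clinic-level restriction factors. Table 1 shows BMI and the baseline questionnaire in both arms; that the questionnaire records age and sex is assumed.
- **Haemoglobin:** use it only if it is available comparably in both arms. Table 1 lists the study test in the intervention arm only, yet a baseline-haemoglobin subgroup is planned for the primary outcome, so its source in control clinics needs to be settled first.
- **Reporting:** always show the adjusted result beside the unadjusted estimate, state which one leads, and do not let observed imbalance add or remove covariates.

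The cost is wording, one extra model and a few degrees of freedom. With 24 clinics in four stratum-by-arm cells there are 24 − 4 = 20, and each clinic-level covariate uses one, which is why that part of the list should be short. Trial status reports enrolment complete, so the change belongs in the analysis plan, dated relative to the first view of data by arm. No new data are needed.

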### Ethics and dissemination

The trial has approval from the Research Ethics Committees of the University of Witwatersrand (approval number: R14/49 M111177); the London School of Hygiene and Tropical Medicine, United Kingdom (approval number: 6099) and the Provincial Research Committees of Gauteng, North West and Limpopo. It is registered with the South African Medicines Control Council as a phase 4 clinical trial (identifier: N2/19/8/2 () #20120157), and with Current Controlled Trials (identifier: ISRCTN35344604 [23]) and the South African registry (identifier: DOH-27-0812-3902).

The trial results will be communicated to stakeholders through dissemination meetings and to trial participants using language-appropriate information sheets. Investigators will present results at relevant conferences, and submit manuscript(s) to peer-reviewed journals. Public access to the participant-level dataset of main trial results and statistical code will be made available.

